## Statistical analysis

Statistical analyses will be performed using STATISTICA 8.0 (StatSoftInc, Tulsa, Oklahoma). Demographic and clinical variables of the two groups of patients will be inspected through descriptive statistics. Independent sample *t*-test (two-tailed) and χ^2^ will be used to assess the differences between the experimental and control training groups at baseline for continuous and categorical variables, respectively, thus allowing us to verify successful randomization. The outcome measure data will undergo a normal distribution assessment using Kolmogorov–Smirnov tests. If the data adheres to a normal distribution, repeated measures ANOVAs will be employed to analyze differences between treatment group (active vs. sham) and across timepoints (T0-T1-T2) on the primary and secondary outcomes. Duncan *post hoc* tests will be performed to follow-up significant interactions and correct for multiple pair-wise comparisons. Conversely, for data not following a normal distribution, the Kruskal-Wallis H test or Friedman test will be applied. The exploratory analysis will center on investigating sex and age differences in treatment response, considering both primary and secondary outcomes. Furthermore, in light of findings on hemisphere-specific tVNS effects cortical excitability (20) and electrophysiological readiness potentials (52), we will conduct a sensitivity analysis. This analysis will examine potential differences in tVNS effects when administered ipsilateral or contralateral to the side of the most affected limb. Statistical significance will be denoted by *p* < 0.05. As to what concerns missing data, a modified intention-to-treat analysis approach will be adopted, including in the analyses all the participants who had completed the pre- and post-treatment evaluation sessions, even if they had not completed all the training sessions. No imputation of missing data, however, will be used considering the limited sample size and observation points.

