In the last years, transcutaneous VNS (tVNS) has been proposed as a noninvasive and patient friendly method to stimulate the vagus nerve, through the skin, by delivering weak electric current to the sensory afferent fibers of the auricular, thick-myelinated, branch of the vagus nerve in the outer ear (19). Such stimulation activates the auricular branch of the vagus nerve and, via this pathway, the nuclei of the nerve located in the brainstem, enhancing brain GABA (20) and Noradrenaline (21) levels, which plays a pivotal role in brain plasticity (22). Since neuroimaging (23) and neurophysiological (20) studies suggested that the effect of tVNS on brain activity is quite similar to the effect induced by traditional, invasive VNS, tVNS has been proposed for the treatment of different clinical conditions including that consequent to stroke (24–30).

Considering the effectiveness of VNS in improving motor function following stroke in adults (18), the present study aims to investigate the effects of tVNS in the pediatric population with CP. The application of non-invasive brain stimulation (NIBS) techniques, such as tVNS, is encouraged also in pediatric populations (31, 32), with prior research indicating that NIBS modalities are generally safe and well tolerated also in children with brain injury (33–35).

With the present trial, we aimed at testing the boosting effects of tVNS when paired with an intensive bimanual training on motor functions in children and adolescents with CP.

Two groups of patients will receive active or sham tVNS paired with the HABIT-ILE protocol. In both groups, the intensive bimanual training will aim to the achievement of the goals that the children and their parents choose themselves, therefore tailored to patients’ needs and highly motivating.

We hypothesize, for both groups, an improvement after the training in the clinical assessments of hand motor ability and daily functioning. However, we also expect that patients treated with HABIT-ILE Training paired with active tVNS will show a greater and more lasting improvement compared to the patients receiving the HABIT-ILE protocol paired with sham tVNS (36). Furthermore, we anticipate that patients will not experience major adverse events due to tVNS (34).

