
## Sample size calculation

Using the GPower 3 software (51) with the “as in SPSS option” we estimated that, with a mixed design comprising the between group factor (active group vs. sham group) and the within variable (Pre T0-, post T1-, follow-up T2, numerator DF = 2), a sample of 22 subjects per group allows detecting, with a power of 0.80 and an alpha level set at 0.05, a between group difference between active and sham tVNS combined motor training of moderate to large effect size [f (U) = 0.35], which is expected to lead to a clinically-relevant improvement in motor activity and dexterity.

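### The plan points to the group-by-time interaction but never names it, or any visit, as deciding a primary outcome, and the power statement, non-normal fallback and analysis set do not all fit it

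*Protocol article*

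**What the plan says.** - **Analysis (Statistical analysis).** For normally distributed outcomes, "repeated measures ANOVAs will be employed to analyze differences between treatment group (active vs. sham) and across timepoints (T0-T1-T2". The threshold is the same everywhere: "Statistical significance will be denoted by" p < 0.05. Duncan tests are reserved for following up significant interactions. Non-normal outcomes go to the Kruskal-Wallis or Friedman test.
- **Analysis set (same section).** Children with the pre- and post-treatment assessments are included, and missing values are not imputed.
- **Power (Sample size calculation).** The calculation covers a group factor and "the within variable (Pre T0-, post T1-, follow-up T2, numerator DF = 2". It arrives at 22 children in each arm for 80% power at a 5% alpha and f(U) = 0.35. The effect to be detected is worded as "a between group difference between active and sham tVNS combined motor training of moderate to large effect size".
- **Hypothesis (Introduction).** Children on active stimulation "will show a greater and more lasting improvement compared to the patients receiving the HABIT-ILE protocol paired with sham tVNS". The size and the persistence of the benefit are both claimed and are not ranked.

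No section names a primary time point or a deciding effect within an outcome.

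**The concern.** This point is about a single outcome, not about how many primary outcomes there are. A 2 × 3 repeated measures ANOVA returns a group effect (1 df), a time effect (2 df) and a group-by-time interaction (2 df). Only the group effect and the interaction compare the arms, and they ask different questions. The group effect averages over all three visits, including T0, before any treatment is given. The interaction asks whether change over time differs between arms.

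If the deciding test is left implicit, the choice can be made after the data are seen, and the conclusion may depend on it. The power statement adds to the doubt because its words describe one test and its degrees of freedom describe another.

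**Working it through.** **Inputs.** From the Sample size calculation: N = 44, k = 2 groups, m = 3 visits, f(U) = 0.35 with the SPSS option, alpha 0.05, numerator DF = 2. The within-child correlation is not given and is varied below, with compound symmetry, normal data and independent children assumed.

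**1. Which test was powered?**
- Interaction: lambda = f(U)² × (N − k) × (m − 1) = 0.1225 × 42 × 2 = 10.29, on 2 and 84 df. Power is 0.812, so the stated 0.80 is reproduced (43 children would give 0.802).
- Group effect at the same f(U): lambda = 0.1225 × 42 = 5.145, on 1 and 42 df. Power is 0.601, and 0.80 would need 68 children.

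So 22 per group was sized on a 2-df within-type test, although the sentence calls it a between-group difference.

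**2. Does the choice matter under the planning effect?** Take a benefit d (in SD units) of equal size at T1 and T2, with d set so that the interaction has lambda = 10.29. Centring (0, d, d) gives a sum of squares of (2/3)d². So 11 × (2/3) × d²/(1 − rho) = 10.29, and d²/(1 − rho) = 1.403.
- Group effect: lambda = (44/3) × d²/(1 + 2·rho), which is 5.15, 2.57 and 0.74 at rho = 0.5, 0.7 and 0.9. Power is 0.60, 0.35 and 0.13.
- T0-to-T1 change difference: lambda = 5.5 × 1.403 = 7.72 on 1 and 42 df, whatever rho is. Power is about 0.77.

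In a separate simulated case (0.6 SD benefit at T1 and T2, rho = 0.7), the group effect was significant in 30% of trials and the interaction in 74%. The two verdicts disagreed in 59%.

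**3. False-positive rate per outcome.** Null simulation, 22 per arm, 100,000 trials at each rho from 0.3 to 0.9, every test at 0.05:

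| Rule for success | Rate |
|---|---|
| Interaction only | about 5% |
| Interaction first, then T1 or T2 change | 4.0–4.2% |
| Group effect or interaction | 9.6–9.9% |
| T1 or T2 change, no gate | 9.0–9.2% |

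The third row is close to the value for two independent tests, 1 − 0.95² = 9.75%.

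**4. Does the rest of the plan fit the interaction?**
- *Fallback.* Kruskal-Wallis compares groups on one measurement per child. Friedman compares visits within children and ignores arm. Neither tests group-by-time, so for a non-normal outcome the implied target and its gate both disappear, and the visit or change score to compare is not stated.
- *Analysis set.* A child with T0 and T1 but no T2 belongs to the analysis set, yet cannot enter a three-visit ANOVA without imputation.

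**The case against.** The strongest reply is that the plan already implies the interaction. Numerator DF = 2 cannot belong to a two-arm group effect. Pairwise tests come only after a significant interaction. The Introduction predicts a greater improvement, and the Discussion speaks of modulating the changes that training induces; both are statements about difference in change. On that reading the power statement is only loosely worded, the error per outcome is about 5%, and ungated tests of T1 and T2 have no place in the ANOVA branch. A condensed article may also leave the order of contrasts to the analysis plan.

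Most of this stands. A reader might infer that the plan runs at about twice its stated 5%. The document does not support that: no sentence lets the group effect count as success, and the Duncan gate rules out free-standing visit comparisons for normal data. A reader might also infer that the trial has only 60% power. That would follow only if the group effect were the deciding test, which DF = 2 contradicts.

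The reply does not remove the point. The interaction is never stated to be decisive, the power sentence describes something else, the fallback cannot deliver an interaction test, and the analysis set is built on two visits rather than three. These are features of what is written, not details awaiting a fuller plan.

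**Conclusion.** The point holds as an unresolved choice of deciding test, not as a demonstrated error inflation. The text leans to the 2-df interaction without making it binding, and three of its own elements do not fit it.

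If the interaction is binding, the error per outcome is about 5%. About 9–10% is a conditional maximum, reached if the group effect is also accepted as success or if T1 and T2 are tested without a gate, which the fallback leaves open. The power figure is sound for the interaction (0.81) and would not be for the group effect (0.60 at the same f(U)).

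The error rates and the 0.77 for T1 change assume normal data, compound symmetry and independent children; the 0.77 also assumes equal benefit at T1 and T2. Randomization by pair and the multiplicity over primary outcomes are left out. The change is worth making before any unblinded analysis.

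**What to change.** State one deciding test per primary outcome and label the ANOVA group main effect descriptive, since it averages in T0. Two forms would serve:

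- **(a)** Name the group-by-time interaction, on which 22 per group was sized. Only if it is significant, test the between-group differences in T0–T1 and T0–T2 change. This keeps the stated power. The plan must then say how children without T2 are handled.
- **(b)** Name the between-group difference in T0–T1 change, which matches the T0-plus-T1 analysis set, and test T0–T2 change only if the first is significant. Power must be restated at about 0.77 under the planning assumptions, and a benefit seen only at T2 could no longer be claimed as confirmatory.

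In either case:
- Carry the same target into the non-normal fallback, for example a rank test on change scores. Under (a), say how the two change scores are combined or ordered, because one rank test covers only one of them.
- Reword the Sample size calculation so that it names the test its power refers to.

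The cost is wording only, with no extra children or data. The one statistical price is the lower power and the lost T2-only claim under (b).

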## Design

This clinical trial represents one of the two Randomized Clinical Trials (RCT) of the project “Bottom-up and tOp-down neuromOdulation of motor plaSTicity in cerebral palsy” (BOOST; FRRB 3438840). The study is a randomized, double-blind, sham-controlled pre-post-test study involving 44 children and adolescents with CP. Patients will be treated in pairs, with a matching of motor deficit severity, IQ, or age, by meeting at least two out of these three criteria. Motor severity will be defined on the basis of the Manual Ability Classification System (MACS) level and classified as low to middle (I-II level) or as middle to high (II-III). With respect to age, two group levels will be identified for children (from 6 to 11 years old patients) and adolescents (12–17 years old patients). With respect to IQ, low IQ value (from 50 to 70) and high IQ value (> 71) will be distinguished. Each pair will be randomly assigned to the active or to the sham tVNS group. The randomization will be stratified based on IQ, MACS level, or age. As for the matching within each pair, at least two out of these three criteria must be encountered.

Both groups will undergo a bimanual training in an ecological and highly motivating environment while carrying out bimanual tasks, including recreational play activities during the application of the tVNS protocol. During the training, starting from a set of proposals the choice of the type of activities to be practiced in each session will be left to patients, boosting the motivational aspect of the training. This will also ensure an individualized and goal-directed approach. The therapists will monitor and modify the activities within each pair to ensure that the intervention maintains the quality of the individualized intervention. The positions performed during bimanual tasks and the activities of daily living will be designed to systematically engage postural control of the trunk and lower limbs according to Habit-ILE protocol. The training will be carried out by a therapist with expertise in maintaining the 1:2 ratios. Training activities will be carried out for 5 consecutive days for 3 h/day for 2 weeks (30 h of intervention overall). Children and adolescents will be assessed 1 or 2 days before the start of the treatment (T0), 1 or 2 days after the end of the treatment (T1), and at a follow-up after 3 months (T2).

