**Figure 1 fig1:**
[figure not shown]
Flow chart of patient’s inclusion and experimental procedures. ^*^The PedsQL and VABS-II will be administered only at T0 and T2, while all other measures will be administered at all timepoints.

Each pair of patients will be randomly assigned to one of two groups (active vs. sham group) with an allocation ratio 1:1, through a computer-generated blocked randomization procedure conducted by independent personnel not directly involved in performing the intensive training. The patients and their parents, the personnel responsible for conducting the bimanual training and analyzing clinical data will be kept blind to the group allocation. Instead, the coordinator of the study and the personnel administering the tVNS will be “not blind.” With respect to the clinical assessment, the staff administering and scoring the scales will be blinded to group allocation. Questionnaire scores and neuropsychological tests will not contain personal information about the patients, who will be identified by an alphanumeric code. All records that contain names or other personal identifiers, such as informed consent forms, will be stored separately from study records identified by code number. In order to uphold the overall quality and credibility of the clinical trial, instances of code breaks should be limited to exceptional circumstances, where knowledge of the actual treatment is deemed absolutely necessary for the ongoing management of the patient. The intensive treatment will take place at the Scientific Institute, IRCCS E. Medea in Bosisio Parini (Lecco, Italy; study sponsor), Fondazione Mondino IRCCS in Pavia (Italy), and ASST Ospedali Civili in Brescia (Italy). The SPIRIT checklist used for protocol reporting can found in the Supplementary material.

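### T0 is analysed as an outcome level rather than as a covariate, which is valid but gives up precision, and the baseline significance tests cannot verify the randomisation

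*Protocol article*

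**What the plan says.** The Statistical analysis section of the protocol article fixes the model for normally distributed primary and secondary outcomes: "repeated measures ANOVAs will be employed to analyze differences between treatment group (active vs. sham) and across timepoints (T0-T1-T2"). Duncan tests follow significant interactions. No covariate is named. The Sample size calculation section uses the same three-level time factor with numerator df 2, and states that "a sample of 22 subjects per group allows detecting" a "moderate to large effect size [f (U) = 0.35"], "with a power of 0.80 and an alpha level set at 0.05", under the G*Power "as in SPSS option".

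The Statistical analysis section also plans t-tests and chi-squared tests between the groups at baseline, "thus allowing us to verify successful randomization".

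The Design section says "The randomization will be stratified based on IQ, MACS level, or age", with pairs as the unit allocated. It also says that all primary and secondary outcomes are collected at every time point, except PedsQL and VABS-II, which are collected at T0 and T2 only.

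**The concern.** T0 is measured before treatment and cannot carry a treatment effect. When it enters as an outcome level, the group-by-time test compares changes from T0, so all of the T0 measurement noise goes into the contrast. With T0 as a covariate, only the part of T0 that predicts the later scores is removed. The sample is fixed at 44 children and the trial is sized close to 0.80, so this precision is worth having.

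The baseline tests add no protection. If allocation was done properly, any baseline difference is chance by construction. A non-significant result does not show that allocation was sound, and a significant one changes nothing in the planned analysis.

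The three-visit model also cannot be run as written for VABS-II and PedsQL, which have no T1 value.

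**Working it through.** **Inputs from the article.** N = 44 (22 per group), alpha 0.05, f(U) = 0.35, three time points, numerator df 2.

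**Assumed.** Compound symmetry with correlation r between visits, shown for 0.5 to 0.9. Children are treated as independent, as the article's own calculation does.

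**Step 1: the plan's own figure.** For the within-between interaction under this G*Power option, error df = (44 − 2) × 2 = 84 and lambda = 0.35² × 84 = 10.29. The noncentral F with 2 and 84 df gives power 0.812. N = 42 gives lambda 9.80 and power 0.791, so 44 is the smallest even N that reaches 0.80. The stated sample size reproduces.

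**Step 2: covariance of the two post-treatment scores (SD 1).**
- As changes from T0: (1 − r) × [[2, 1], [1, 2]].
- Conditional on T0: (1 − r) × [[1 + r, r], [r, 1 + r]].

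**Step 3: gain in noncentrality.**
- Equal effect at T1 and T2. The information is 2/(3(1 − r)) for changes and 2/((1 − r)(1 + 2r)) given T0. The ratio is 3/(1 + 2r).
- Effect at one visit only. The information is 2/(3(1 − r)) for changes and (1 + r)/((1 − r)(1 + 2r)) given T0. The ratio is 3(1 + r)/(2(1 + 2r)).

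The change covariance equals the conditional covariance plus (1 − r)² in every cell. The gain is therefore largest when the effect is the same at both visits. For effects in the same direction it is smallest when the effect is at one visit only.

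**Step 4: power of the 2-df test**, with lambda = 10.29 × ratio and error df 2 × (44 − 3) = 82. The starting value is 0.812 in every row.

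| r | ratio, equal effects | lambda | power | ratio, one visit | lambda | power |
|---|---|---|---|---|---|---|
| 0.5 | 1.50 | 15.43 | 0.942 | 1.125 | 11.58 | 0.858 |
| 0.7 | 1.25 | 12.86 | 0.894 | 1.063 | 10.93 | 0.836 |
| 0.8 | 1.15 | 11.87 | 0.867 | 1.038 | 10.69 | 0.827 |
| 0.9 | 1.07 | 11.02 | 0.840 | 1.018 | 10.47 | 0.819 |

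With equal effects, the variance of the T1/T2-mean contrast falls to (1 + 2r)/3 of its value: 0.67, 0.80, 0.87 and 0.93.

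**Step 5: what further covariates do.** Simulated power of the 1-df contrast of the T1/T2 mean (6,000 runs per setting). The five extra terms are IQ, MACS, age and two centre indicators, none of them prognostic.

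| r | change from T0 | T0 as covariate | T0 plus five terms |
|---|---|---|---|
| 0.5 | 0.876 | 0.973 | 0.945 |
| 0.7 | 0.879 | 0.930 | 0.894 |
| 0.8 | 0.884 | 0.918 | 0.877 |
| 0.9 | 0.882 | 0.896 | 0.848 |

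At r = 0.8 and 0.9 the long list ends below the unadjusted change contrast. When the three stratification factors explain 30% of the between-child variance, the extra terms still lower power at r = 0.8, from 0.914 to 0.891. The near-free gain therefore belongs to T0 alone.

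The picture differs if a factor predicts change. With an assumed age-group effect on change of 0.3 or 0.5 SD, a further simulation at r = 0.8 gave 0.856 and 0.809 for the unadjusted change, against 0.870 and 0.879 for T0 plus all five terms. Across r = 0.7 to 0.9, T0 plus age group alone gave 0.881 to 0.926.

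**The case against.** The strongest reply is that the planned test is valid, that the trial was sized on it, and that the figure reproduces. Baseline adjustment is then an efficiency preference whose size rests on a correlation nobody has stated. If visits correlate at 0.9 and the effect appears at one visit only, power goes from 0.812 to 0.819. All of this stands and limits the claim. It does not remove it, because the gain is positive for every r below 1 unless the effects at T1 and T2 cancel, and T0 is collected anyway.

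A second reply is that a condensed article leaves covariates to an analysis plan that is not shown. That is fair for the stratification factors. It does not cover T0, because its use as an outcome level is stated text in both the sample size and the analysis sections.

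A reader might infer more than the article supports:
- **Bias from regression to the mean.** Under randomisation it is the same in expectation in both arms. The cost is variance.
- **Chance imbalance in MACS, IQ or age left in the estimate.** These are constant within a child, so their additive effects cancel from the group-by-time test. They matter only if they predict change. The article gives a reason to expect that for age: the Introduction reports better motor gains under 8 years, and the Discussion says effectiveness falls as children grow.
- **A treatment effect diluted by averaging T0 into the group main effect.** Numerator df 2 and the follow-up of interactions show that the main effect is not the test the trial was sized on.
- **A standard error misstated because the randomisation factors are left out.** No calculation supports this here.
- **Centre as a required term.** The article lists three sites but does not name centre as a stratification factor.

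**Conclusion.** The point holds as a loss of efficiency. With the same 44 children, moving T0 from outcome to covariate raises the power of the 2-df test from 0.81 to between 0.84 and 0.94 if the effect is equal at T1 and T2. It raises it to between 0.82 and 0.86 if the effect is at one visit only. Both ranges run over r = 0.9 down to 0.5. The equal-effect range is the most favourable case. The hypothesis of a larger and more lasting improvement does not by itself imply equal effects.

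All figures rest on compound symmetry, an assumed r and independent children. Pairs are allocated and trained together, so positive within-pair correlation would lower every figure, before and after the change. The figures are for T0 adjustment alone and do not carry over to a model with a long covariate list.

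Separately, the claim that baseline tests verify the randomisation is wrong and should go.

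**What to change.** 1. For each outcome measured at all three visits, model T1 and T2 with the T0 score as covariate and with group, visit and group-by-visit terms. A longitudinal model that constrains the arm means to be equal at T0 serves equally well.
2. For VABS-II and PedsQL, compare the arms at T2 adjusted for T0.
3. Add at most a short pre-specified list of the stratification factors, age group first. Their purpose is to match the analysis to the randomisation, and they may cost some power if they are not prognostic. Centre is not required.
4. Before MACS class is used, reconcile its definition in the Design section, where level II falls in both classes.
5. Replace the baseline tests with a descriptive baseline table, and remove the statement that they verify the randomisation.

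The cost is a change of analysis wording and one degree of freedom per visit for T0, plus one for each two-level factor added. No new data are needed. The change should be made before unblinding.

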#### The visuomotor task

This is an *ad hoc* computer-based task for the evaluation of manual visuomotor control. It involves a mouse click-and-drag operation where an object appears at the center of the screen. The objective is to drag and drop the object to the location indicated by a previously presented arrow, pointing toward a target object within a configuration of objects. Participants are required to focus on the direction of the arrow, swiftly and accurately moving the central object to its designated target location, by using a mouse with the less affected hand. This task enables the measurement of movement time (MT, in milliseconds; consisting in the time necessary to move the object in the target position); precision error (calculated as the distance, in pixels between the drop position of the object and the actual target position); the proportion of overtime errors (the percentage of trials in which responses are too slow). Smaller values of Movement time, Precision error and overtime errors indicate better performance.

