## Discussion

Task-specific training, which are goal and functional oriented, are the most promising approach for the treatment of CP (9). Though, available evidence suggested that the effectiveness of these interventions decreases as the children grow (3). Thus, there is an urgent need to identify the most effective rehabilitation approaches that confer the greatest clinical gain, not only in the youngest, often “over-treated” children, but also in more chronic conditions, as for older children and adolescents with CP, using new forms of intervention that may adjuvate the rehabilitation by boosting brain plasticity.

The current trial aims at filling this gap, by proposing a protocol that can be individualized on patients’ needs and that will exploit neural plasticity as induced by tVNS. In this trial, 6–17 years old aged patients with unilateral or bilateral CP will be treated in pairs, with a matching of motor deficit severity, IQ, or age. Each pair will be randomly assigned to the active or to the sham tVNS group. During the application of the active or sham tVNS protocol, both groups will undergo a bimanual training according to the Habit-ILE protocol, which train bimanual tasks, including recreational play activities, while systematically engaging postural control of the trunk and lower limbs in an ecological and highly motivating environment. Training activities will be carried out for 2 consecutive weeks, 5 days per week, for 3 h/day, with an overall dose of 30 h of intervention. TVNS will be applied for the first 75 min in each session. As primary outcome measures, we will quantify the improvements in manual visuomotor control. Secondary outcomes will instead encompass a comprehensive assessment of motor skills, functional adaptation, and quality of life. Safety and tolerability will be evaluated too.

The study design provides for an active control group that will receive sham tVNS during participation to the training, thus accessing a treatment that represents the gold standard for CP. The comparison between the two groups will allow us to test the specific, modulatory effects on tVNS on the changes induced by the training. At the same time, it will allow us to test the transferability into everyday life adaptive behavior and quality of life.

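### For non-normal outcomes the plan swaps the group-by-time ANOVA for Friedman, which ignores arm, or Kruskal-Wallis, without saying what it compares

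*Protocol article*

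**What the plan says.** The Introduction sets out two expectations. The first concerns training: "We hypothesize, for both groups, an improvement after the training in the clinical assessments of hand motor ability and daily functioning". The second is the trial's question, that children given active stimulation "will show a greater and more lasting improvement compared to the patients receiving the HABIT-ILE protocol paired with sham tVNS". The Discussion says where the answer lies: "The comparison between the two groups will allow us to test the specific, modulatory effects on tVNS on the changes induced by the training".

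The Statistical analysis section has two branches. The screen is: "The outcome measure data will undergo a normal distribution assessment using Kolmogorov–Smirnov tests". If normality holds, "repeated measures ANOVAs will be employed to analyze differences between treatment group (active vs. sham) and across timepoints (T0-T1-T2", and "Duncan *post hoc* tests will be performed to follow-up significant interactions". If it does not: "Conversely, for data not following a normal distribution, the Kruskal-Wallis H test or Friedman test will be applied". The section does not say which of the two tests serves which contrast, at which visit, or whether it is run on raw scores or on change.

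The screen applies to primary and secondary outcomes alike. The primary set includes a bounded percentage within the visuomotor task: "the proportion of overtime errors (the percentage of trials in which responses are too slow".

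**The concern.** The two branches do not test the same thing. The ANOVA branch reaches the trial's question through the group-by-time interaction. In the other branch, Friedman compares visits within children and takes no account of arm. Kruskal-Wallis compares independent groups on one value per child, and its meaning depends on which value is supplied. Joining them with 'or' offers tests of two different hypotheses as if they were interchangeable.

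A primary outcome that fails the normality screen could therefore be reported with a p-value for the shared training gain, or with a between-arm comparison of raw post-treatment scores that makes no use of T0. If all visits were pooled, the between-arm test would also be invalid, because it would treat repeated measurements as independent.

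**Working it through.** **1. Which effect the trial is sized on.** Inputs from Sample size calculation: 22 per group (N = 44), f(U) = 0.35, alpha 0.05, numerator DF 2, the 'as in SPSS' option. For the group-by-time interaction with k = 2 groups and m = 3 visits:

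- λ = f(U)² × (N − k) × (m − 1) = 0.1225 × 42 × 2 = 10.29
- df1 = (2 − 1)(3 − 1) = 2; df2 = 42 × 2 = 84
- power = 0.812

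The stated 0.80 with 22 per group reproduces. A between-group main effect would have power 0.60, so the design rests on the interaction.

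**2. Simulation set-up.** 22 independent children per arm, three visits, equal correlation ρ between visits, 2,000 to 4,000 trials per scenario. The protocol gives no SDs, correlations or expected gains, so all of these are assumptions.

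**3. No tVNS effect, both arms gain from training.**

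- Friedman on all children, gains of 0.4 to 0.6 SD, ρ 0.7 to 0.8: rejects in about 86% to 100% of trials (a repeat run gave 84% to 100%).
- The remaining figures use a gain of 0.5 SD and ρ 0.6 to 0.9:
  - Kruskal-Wallis between arms on raw T1 scores: 0.048 to 0.060, valid.
  - Kruskal-Wallis between arms on T1 − T0 change: 0.042 to 0.053, valid.
  - Kruskal-Wallis between arms with all visits pooled: 0.15 to 0.24, invalid.

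**4. Power with a real, sustained tVNS effect.** For an added effect d (in SD units) present at T1 and T2, λ = n d² / [3(1 − ρ)] with n = 22. Setting λ = 10.29 gives d = √[3 × 10.29 × (1 − ρ) / 22]:

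- ρ = 0.7: d = 0.65
- ρ = 0.8: d = 0.53
- ρ = 0.9: d = 0.375

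Power of Kruskal-Wallis on raw T1 scores, for log-normal outcomes with an additive effect:

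| Skew (log-scale SD) | ρ 0.7 | ρ 0.8 | ρ 0.9 |
|---|---|---|---|
| Mild (0.5) | 0.74 | 0.56 | 0.33 |
| Strong (1.0) | 0.97 | 0.92 | 0.75 |

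A rank test on T1 − T0 change has about 0.83 to 0.98 over the same scenarios, with the lower end under mild skew and the upper end under strong skew. Repeat runs moved the tabulated figures by at most about 0.05. The loss from raw scores is therefore large at high correlation with mild skew, and small or absent at ρ 0.7 with strong skew.

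**5. Sensitivity to the form of the effect.** Suppose tVNS multiplies a skewed score instead (0.4 SD on the log scale added to a shared 0.5 SD gain, ρ 0.6 to 0.9). Power is then 0.23 to 0.25 on raw T1 scores and 0.32 to 0.68 on change.

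**The case against.** The best defence is that the preceding sentence of the plan names two contrasts, group and timepoint, and that the two tests map onto them: Kruskal-Wallis for arms, Friedman for visits. On that reading Friedman answers the separate expectation that both groups improve. Its high rejection rate is then a correct rejection of its own null hypothesis and not an error rate. The choice of response variable could sit in an analysis plan that is not shown.

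Much of this stands. A reader might infer that neither test can assess tVNS. That is false for Kruskal-Wallis, and the wording does not exclude running it on change. A reader might also fear that Friedman will be run in each arm and a significant active arm set against a non-significant sham arm. Nothing in the article proposes that, so no false-positive rate from such a reading can be charged to the plan. Power figures for normal data would show a heavier loss on raw scores, but they do not describe this branch. A Kolmogorov–Smirnov test with estimated mean and SD sends normal data of this size to the fallback in under 0.1% of runs, mildly skewed data in about 8% to 10%, and strongly skewed data in about 71%. Which outcomes will actually fail the screen is not known; the overtime-error percentage is only a plausible candidate.

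The defence does not clear the sentence. The article names the tests itself and offers as an alternative one that cannot compare arms. It drops the interaction without naming a replacement for it. Under Dissemination the authors undertake to follow the procedures in this protocol.

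**Conclusion.** Wrong as written, and worth correcting before analysis, though short of a defect that must be fixed for the trial to be interpretable. Friedman cannot show that tVNS adds to training. Kruskal-Wallis can, if it is applied between arms to change from T0, or validly but in general less efficiently to raw T1 or T2 scores; the plan states neither. The cost of the raw-score choice ranges from almost nothing to more than half the power, depending on skewness and correlation. All simulated figures rest on assumed SDs, gains, correlations and distributions, and treat children as independent. Allocation by pairs is a separate matter that affects every test named. Only outcomes that fail the normality screen are touched.

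**What to change.** Replace the sentence on non-normal data with:

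> If the ANOVA is judged unsuitable, arms are compared by a rank test of change from T0 (Wilcoxon-Mann-Whitney, or rank ANCOVA with T0 as covariate) at T1 and at T2, with the Hodges-Lehmann difference and 95% CI.

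One of the two rank tests should be chosen before unblinding. Keep Friedman, if at all, as a description of within-arm change and state that it is not a test of tVNS. The cost is one sentence in the analysis section, with no new data and no extra patients.
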